### Sample size

Using a non-inferiority design, and based on clinically relevant difference of HbA_1c_ of 0.5%, a standard deviation of 1.5 and groups of 7–8 participants per randomisation group, for 80% power at one-sided 5% significance 150 participants were required to complete the study procedures. Allowing for a 10% drop-out from randomisation to completion of the trial, it was anticipated that we would require 166 subjects to be randomised in the study. Thus we aimed to run 24 courses (12 courses per arm). Each centre was required to recruit 32 patients to enable 4 courses (two standard DAFNE and two 5 week) to be run with 8 participants on each. However, during the recruitment phase of the trial it became apparent that the drop-out rate between randomisation and course participation was higher than had been anticipated, at over 11%, hence one centre ran an extra pair of courses.

The flow of patients through the trial is shown in Figure 1, this figure follows the CONSORT approach, as will future reporting of the trial results [9].

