### Outcomes

We measured outcomes on two occasions primarily to examine the time of maximum effect, and also because repeated measures improves the power to test the main objective.

The Primary outcome was:

Change in HbA_1c_ from baseline at 6 and 12 months. HbA_1c_, a measurement of glycosylated haemoglobin, is regarded as the gold standard measure of glycaemic control reflecting overall blood glucose values over the previous 8–12 weeks. There is a strong relationship between HbA_1c_ and the risk of developing long-term diabetic complications and it is accepted as a reasonable surrogate for long-term outcomes in individuals with diabetes. HbA_1c_ was measured at local laboratories DCCT aligned (as per Diabetes Control and Complications Trial [10]).

The Secondary Outcomes were:

Change in HbA_1c_ from baseline at 6 and 12 months for those with a baseline HbA_1c_ ≥7.5%, This is because some of the participants with low HbA_1c_s would be aiming to reduce the number of episodes of hypoglycaemia, as opposed to further reducing their HbA_1c_.

Biomedical: eGFR, and lipids (including HDL cholesterol), using local labs at baseline and 12 months as part of routine clinical monitoring.

Hypoglycaemia: Number of episodes of severe hypoglycaemia using a standard definition of an episode leading to cognitive impairment sufficient to cause either coma or requiring the assistance of another person to recover. (The number of severe episodes is considered to be reliably recalled by patients for up to 1 year. [11])

Psychosocial:

• Quality of life: Quality of life (QoL) is assessed using both the diabetes-specific quality of life scale (DSQOLS [12]), and the generic measures of QoL, SF-12 [13], and EQ-5D [14].

• Emotional Well-being: is assessed using the Hospital Anxiety and Depression Scale (HADS; [15]), the diabetes-specific Problem Areas in Diabetes Scale (PAID [16]).

• Self-efficacy: Diabetes-specific self-efficacy is assessed using the Confidence in Diabetes Self-Care measure [17] a validated, reliable measure for people with type 1 diabetes.

• Thoughts about Diabetes [Personal Models of Diabetes [18,19]: This assesses beliefs about the seriousness of diabetes and treatment effectiveness. It is validated for use with adults with diabetes [20].

• Self-Care Behaviours: The revised Self-Care Inventory, a measure of perceived adherence to diabetes self-care recommendations [21].

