### Analysis

The primary analysis will be a linear model of HbA_1c_ at 12 months with baseline HbA_1c_ as a covariate, (which will improve the power relative to the predicted power), using generalised estimating equations (GEE) to control for clustering within courses. The intracluster correlation coefficient coefficient (ICC) will be estimated using the method of moments. Poisson regression (or a zero-inflated Poisson regression if necessary) will be used on the number of hypoglycaemic episodes over 12 months, which should also have more power than a dichotomy of having/not experiencing an episode, again using GEE to account for clustering. We will use an intention to treat analysis, but will explore the issue of participants dropping out using multiple imputations. The full analysis set (FAS) for the intention to treat analysis includes all patients for whom baseline data was collected. A per protocol analysis will also be performed.

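### The zero-inflated Poisson fallback for severe hypoglycaemia has no standard GEE form and changes the arm effect being estimated; one pre-specified log-link GEE should be the main analysis

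*Protocol article*

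**What the plan says.** The Outcomes section lists, among the secondary outcomes, "Number of episodes of severe hypoglycaemia using a standard definition of an episode leading to cognitive impairment". For its analysis, the Analysis section says "Poisson regression (or a zero-inflated Poisson regression if necessary) will be used on the number of hypoglycaemic episodes over 12 months". It justifies counts over a yes/no outcome on grounds of power: "which should also have more power than a dichotomy of having/not experiencing an episode". It then adds "again using GEE to account for clustering". The cluster is the course, as the HbA1c sentence just before makes clear: "using generalised estimating equations (GEE) to control for clustering within courses".

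As written, GEE covers both the Poisson model and the zero-inflated alternative. The article gives no episode rate, dispersion or proportion of zeros for this outcome.

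**The concern.** Two things are joined here that do not ordinarily go together. A GEE specifies one marginal mean, a link, a variance function and a working correlation, and takes its standard errors from a cluster-level sandwich. A ZIP is a mixture likelihood: a logit part for structural zeros and a log part for counts among the remaining, susceptible patients. An analyst who reaches the fallback cannot carry the sentence out with a standard GEE and has to improvise.

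There are two consequences. First, the Poisson branch gives one ratio of overall episode rates, while the ZIP branch with arm in both parts gives an odds ratio and a rate ratio among the susceptible, which can point in opposite directions. The switch would depend on the observed counts, so the data would decide which quantity is reported. Second, if the improvisation is an ordinary likelihood fit, the course-level robust variance is lost. At stake is one clear comparison of severe hypoglycaemia rates between the two formats, which bears on the first objective (whether outcomes are comparable).

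**Working it through.** The plan states no figure for this outcome, so there is none to reproduce. The check has a structural part and a simulated part.

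**1. What each branch estimates.** Let π be the probability of a structural zero and λ the mean count among the susceptible, with subscripts 1 and 0 for the arms.

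- Poisson GEE: overall rate ratio = μ1/μ0.
- ZIP zero part: odds ratio = [π1/(1−π1)] / [π0/(1−π0)].
- ZIP count part: λ1/λ0.
- Overall ratio implied by ZIP: [(1−π1)λ1] / [(1−π0)λ0].

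The count coefficient equals the overall ratio only if π1 = π0. In an arm-only ZIP with an interior solution, the score equations set (1−π)λ equal to the sample mean in each arm. The implied overall ratio is then exactly the crude ratio of arm means, which the Poisson model estimates directly.

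**2. Number of clusters.** The Sample size section gives 12 courses per arm, so 2 × 12 = 24. Four courses in each of seven centres gives 7 × 4 = 28. One centre ran an extra pair. The simulations use 24 and 28.

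**3. False-positive rates with no arm difference.** Two-sided 5% tests. Means, dispersions and course effects are assumptions.

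*24 courses of 7, 3,000 runs per row* (simulation error near 5%: √(0.05 × 0.95/3000) ≈ 0.4 points). SD is the course-level SD of the log rate; k is the gamma shape. Percentages:

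| Assumed data | Naive Poisson | Poisson GEE, z | Poisson GEE, corrected, t(22) | ZIP count part, model-based | ZIP count part, course sandwich, t(22) |
|---|---|---|---|---|---|
| True ZIP, mean 0.5, π = 0.7 | 17.7 | 6.8 | 4.7 | 4.4 | 4.8 |
| Same, course SD 0.3 | 22.0 | 7.8 | 4.5 | 7.3 | 5.9 |
| π = 0.5, k = 0.5, mean 0.5 | 30.7 | 8.7 | 5.6 | 19.5 | 7.6 |
| k = 0.3, mean 0.5 | 21.2 | 8.4 | 5.9 | 15.1 | 6.4 |
| Same, course SD 0.3 | 25.7 | 8.6 | 6.4 | 18.1 | 7.5 |
| k = 0.15, mean 1.0 | 47.7 | 9.5 | 7.0 | 39.5 | 8.1 |
| Same, course SD 0.3 | 49.8 | 9.3 | 7.0 | 40.9 | 8.1 |

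In the over-dispersed rows, the model-based ZIP standard error is 0.40 to 0.68 of the true SD. A pure Poisson setting is left out because ZIP could be fitted in only 21% of runs.

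*28 courses of 7, gamma-Poisson counts, 400 runs per setting* (simulation error ≈ √(0.05 × 0.95/400) = 1.1 points). Percentages:

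| Mean, k | Naive Poisson | ZIP count part, model-based | Poisson GEE, bias-corrected |
|---|---|---|---|
| 0.4, 0.15 | 29.0 | 25.8 | 7.7 |
| 0.8, 0.15 | 41.0 | 34.5 | 7.0 |
| 0.8, 0.3 | 26.8 | 28.7 | 4.5 |
| 1.5, 0.2 | 51.2 | 44.8 | 6.0 |

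A repeat of these four settings gave 21–42% for model-based ZIP, 6.7–8.1% for the ZIP count part with course-level sandwich errors, 4.9–6.4% for the corrected Poisson GEE, and about 8–9% for the uncorrected GEE with z-tests. With robust errors, at least one of the two ZIP coefficients was significant in about 9–12% of null trials. That is roughly what two tests produce: if they were independent at 5%, 1 − 0.95² = 9.75%.

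**The case against.** The strongest reply is that the plan keeps GEE for clustering, so a ZIP with model-based errors is not what it describes. A reader might infer that the planned analysis would carry badly understated error bars. The documents do not support that: it requires the analyst to drop the robust variance the text asks for, and over-dispersion to remain among the counts. Nor do two coefficients shrink standard errors. Naive Poisson is worse than model-based ZIP in most settings above, so the lost sandwich is the cause. When the data truly follow a ZIP, even the model-based fit gave only 4.4% without and 7.3% with course effects. All this stands.

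A reader might also infer that ZIP can yield no single rate ratio. That goes too far. If arm enters only the count part, its coefficient is the overall ratio; otherwise the overall ratio can be derived as in step 1. But the article does not call for that derivation, and standard ZIP output does not report it.

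The mismatch is not absolute either: cluster-robust, estimating-equation and marginalised forms of ZIP exist. And the trigger for the switch, the reported contrast and the small-sample correction may properly sit in an analysis plan that is not shown, so their absence is no fault in itself. What remains is what the sentence does state: a model paired with a method that has no standard form for it, and a conditional switch to a different estimand. An analysis plan would have to specify a non-standard version or depart from the sentence.

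**Conclusion.** The point holds as a specification fault with a contingent effect on error rates. The fallback has no standard GEE form, and with arm in both parts it replaces one marginal rate ratio with two coefficients, on the strength of the data. With course-level robust errors kept, each coefficient is near nominal (about 4–8%), and the main cost is an unclear estimand plus about 9–12% false positives if both are tested. With ordinary likelihood fitting, roughly 15–45% is possible, but only under the assumed over-dispersion; the document gives nothing to fix that figure.

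The fallback is also not needed to cope with excess zeros. A log-link GEE with robust errors remains valid for the marginal rate ratio, and with the small-sample correction it rejected 4.5–7.7% across the settings examined. The outcome is secondary, and the HbA1c conclusion is unaffected.

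**What to change.** Make the main analysis of severe hypoglycaemia one pre-specified log-link GEE, with Poisson or negative binomial variance, clustered on course. Use small-sample-corrected robust errors, since there are only about 24–28 courses, and report one rate ratio with its confidence interval. Remove the conditional switch. If ZIP is kept, make it a sensitivity analysis with course-level robust errors that reports the overall mean ratio rather than the two separate coefficients.

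The cost is a change of analysis wording; no data collection or sample size is affected. The downside is a slight loss of efficiency if the counts truly follow a ZIP.

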Some non-DAFNE centres have reported outcomes during routine care in self-selected individuals which are comparable to those reported in the original DAFNE trial [7]. Yet, since observational data of this type are prone to bias it is unclear whether such an extended approach to skills training is as effective as that provided on a 1 week intensive course. This randomised control trial is designed to test the hypothesis that the benefit of a structured education programme, with the identical contact time, is the same whether delivered over 1 or 5 weeks.

There are theoretical reasons why the two approaches might lead to different outcomes. A 1 week model might lead to stronger peer support developing over the week that could help to improve incorporation of self-management skills. Alternatively, a course delivered over 5 weeks might allow patients to gain more practice in self-management skills during the weeks between education sessions, thus facilitating integration of its principles into everyday life, and hence enhance sustainability. However, the potentially weaker peer support on a 5 week course may lead to a higher drop-out rate, with less participants completing the full 5 days of skills training.

Establishing whether DAFNE delivered at weekly intervals is as effective as delivering it over 5 consecutive days will help guide and inform decisions about future course delivery. Potentially it could also allow more individuals with Type 1 diabetes to receive structured education and increase patient choice. As qualitative work can provide important insights into trial outcomes [8], a qualitative sub-study was conducted in which we drew upon people’s understandings and experiences, by interviewing both educators and course participants. We also surveyed participants at the end of the trial asking whether they would prefer future structured education programmes to be delivered over 1 week or a more extended period of 5 weeks. Included in this survey were questions enquiring as to current self-management strategies.

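### The primary model is a GEE on one 12-month HbA1c per person, so as written it covers only patients with that value, although the declared intention-to-treat set is everyone with baseline data

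*Protocol article*

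**What the plan says.** All references are to the protocol article.

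- **Analysis, set.** The full analysis set for intention to treat "includes all patients for whom baseline data was collected". Under Randomisation, baseline data come before allocation, so this set is in effect everyone randomised.
- **Analysis, model.** The primary model regresses 12-month HbA1c on arm and baseline HbA1c, with GEE for clustering by course. Each person contributes one outcome value.
- **Analysis, drop-out.** "We will use an intention to treat analysis, but will explore the issue of participants dropping out using multiple imputations". A per-protocol analysis is also planned.
- **Outcomes.** HbA1c is measured at 6 and 12 months, partly because repeated measurement is said to raise power for the main objective.
- **Sample size.** "Using a non-inferiority design, and based on clinically relevant difference of HbA_1c_ of 0.5"%. The allowance for loss was set thus: "Allowing for a 10% drop-out from randomisation to completion of the trial". Later, "the drop-out rate between randomisation and course participation was higher than had been anticipated, at over 11"%, and one centre ran an additional pair of courses.
- **Background.** Weaker peer support on the 5 week course "may lead to a higher drop-out rate, with less participants completing the full 5 days of skills training".
- **Follow up.** The 6- and 12-month visits are counted from the final course day.

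**The concern.** The set, the model and the role of imputation do not fit together. A GEE on one outcome per person drops anyone without that outcome unless it is imputed, and imputation is set apart as something to explore. The headline estimate would then describe patients with a 12-month HbA1c, not the declared set. A patient seen at 6 but not at 12 months would contribute nothing, although the second measurement is justified in part by its gain in power.

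Patients who never started a course fit least well. They have no final course day from which to time the 12-month visit, and no attended course to act as their GEE cluster. The additional courses restore numbers but do not bring these patients into the analysis.

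What is at stake is the non-inferiority conclusion. If the 5 week arm loses more patients and those patients fare worse, leaving them out flatters that arm.

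**Working it through.** **The plan's own loss allowance.** 150 / (1 − 0.10) = 166.7, which agrees with the stated 166 apart from rounding. The 150 itself is not reproduced: 2 × (1.645 + 0.842)² × 1.5² / 0.5² gives 112 per arm, 224 in total, before clustering or baseline adjustment. That is a separate matter and does not decide this point.

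**How many patients are in question.** The Abstract gives 213 randomised. Assume the 11% applies to all of them: 0.11 × 213 = 23.4, so at least 23 members of the full analysis set did not take up a course. If none of them has a 12-month HbA1c (also an assumption), at most 213 − 23 = 190 enter the primary model before any later loss.

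**Precision.** With SD 1.5, one-sided 5%, margin 0.5%, true difference zero, equal arms and no clustering or covariate gain, power = Φ(0.5 / (1.5 × √(4/N)) − 1.645):

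- N = 213: about 78%
- N = 190: about 74%
- N = 170 (20% missing, assumed): about 70%

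Baseline adjustment raises these figures and clustering lowers them; the fall from one to the next is the point.

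**Bias.** Let p5 and p1 be the missing shares in the 5 week and 1 week arms. Let g5 and g1 be the amounts by which missing patients' HbA1c exceeds that of observed patients in the same arm, after baseline adjustment. The mean for a whole arm is its observed mean plus p × g, so the observed-only analysis understates the 5 week arm's disadvantage by

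p5 × g5 − p1 × g1.

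The article gives none of these four quantities. On assumed values:

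| Scenario | Calculation | Bias (% HbA1c) | Share of 0.5% margin |
|---|---|---|---|
| Equal loss, equal gap | p5 = p1, g5 = g1 | 0 | 0 |
| 20% v 10% missing, same gap of 0.5 to 1.0 | (0.20 − 0.10) × 0.5 to 1.0 | 0.05 to 0.10 | 10 to 20% |
| 11% missing in each arm, gap larger by 0.5 to 1.0 in the 5 week arm | 0.11 × 0.5 to 1.0 | 0.055 to 0.11 | 11 to 22% |
| 20% v 10% missing, only 5 week missing patients worse | 0.20 × 0.5 to 1.0 | 0.10 to 0.20 | 20 to 40% |

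The last row needs an extra assumption and is an outer case. Reversing the arms reverses the sign. In the second row the gap would have to be 0.5 / 0.10 = 5.0% HbA1c to use up the whole margin. Bias of this kind therefore matters only when the confidence limit lies fairly close to the margin.

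**The case against.** The article never says that the primary model is limited to observed values. It names intention to treat, a full analysis set, multiple imputation and a per-protocol analysis, and the details of imputation usually belong in an analysis plan, which is not shown here. This stands in part: the restriction is inferred from the form of the model, and it would be wrong to say that the intention-to-treat label is false of the result. But the article does fix the set, the model and an exploratory role for imputation, and these conflict on the page.

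A reader might infer that the plan predicts more loss in the 5 week arm and that the 11% confirms it. The documents do not support that. The Background says only that it may happen, within a list of theoretical reasons running both ways, and it speaks of completing the course, not of missing HbA1c. The 11% arose before any course, so peer support on a course cannot explain it. It is not split by arm, and those patients are not said to lack a 12-month value.

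Nor is the direction of bias known. Equal loss with equal gaps gives none, and including untreated non-attenders from both arms tends to pull the arms together, itself towards non-inferiority. The planned per-protocol analysis is a proper companion in a non-inferiority trial, but it recovers no missing outcome in the full analysis set.

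Finally, standard imputation and likelihood models assume missing at random, so making one primary does not by itself remove bias from drop-outs who do worse than similar completers. That is correct, and it is why the fix has a second part.

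**Conclusion.** The point holds as a mismatch between the declared set and the primary model, together with unused 6-month data. It does not show that the trial's result is biased. Bias towards non-inferiority is conditional on p5 × g5 exceeding p1 × g1 after baseline adjustment. The illustrative size, 0.05 to 0.10% HbA1c or 10 to 20% of the margin, rests wholly on assumed missingness of 20% against 10% and an assumed common gap of 0.5 to 1.0%. The change is worth making because it uses data already collected and brings the primary estimate into line with the set that the article names.

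**What to change.** 1. **Primary estimate.** Use a two-visit likelihood model of 6- and 12-month HbA1c, or multiple imputation, on all randomised patients in their allocated arm. Take the allocated course as the cluster whether or not it was attended; Recruitment procedures says participants were told a pair of course dates beforehand, so an allocated course should be identifiable. Inform the missing values with baseline and 6-month HbA1c, attendance, arm and centre. Attendance arises after randomisation, so it belongs in the imputation model and not in the model that estimates the arm effect. The definition of the set need not change.

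2. **Sensitivity analysis.** Pre-specify a non-inferiority analysis that worsens imputed 5 week values by 0.25%, 0.5% and 1.0% and reports the tipping point at which non-inferiority is lost. With 20% of that arm imputed (assumed), the arm difference moves by 0.20 × 0.25, 0.5 and 1.0 = 0.05, 0.10 and 0.20%. This part carries most weight for patients who never started a course, who may have no 6-month value either.

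3. **Reporting.** Give, by arm, the numbers who did not start a course and the numbers with a 6-month and a 12-month HbA1c. Keep the per-protocol analysis beside the primary one.

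Searching local laboratory records for missing HbA1c values should not be planned unless consent is confirmed to cover it; the article records written consent but not its scope.

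The cost is extra analysis work, no new visits, and a possibly less favourable non-inferiority result. The Discussion places the analysis in the future, so the choice should be fixed before it begins.

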### Health economics analysis

An economic evaluation will be undertaken from the NHS perspective, using both a within trial timeframe and a modelled patient lifetime timeframe. The modelled analysis will be the primary focus of the economic sub-study. Patient costs will be calculated covering training, equipment, drugs and NHS contacts relating to the management of diabetes and its associated conditions. The cost of the training associated with the control and intervention groups will be calculated through a survey of resource use and costs at each of the seven recruiting centres. The survey will cover staff input, consumables, capital and overheads, and will be followed up with discussions with staff at each centre to ensure the quality of information provided.

Patient-level data will be collected for equipment, drugs and NHS contacts. Equipment and drug use will be taken from the trial’s clinical record forms, while the NHS contacts will be taken from the DAFNE Programme’s patient database. This database records all primary care contacts relating to diabetes, specific contacts for hypoglycaemic events, and diagnosis-specific inpatient admissions.

Unit costs will be taken from standard sources (NHS Reference Costs, British National Formulary, and PSSRU). Quality adjusted life years (QALYs) will be estimated using EQ-5D at baseline, 6, and 12 months, and patient mortality.

Two analyses, one within the trial, and another using a lifetime analysis based on the Sheffield Type 1 Diabetes Policy Model (currently in development through the NIHR Programme Grant), will be undertaken. An incremental cost effectiveness ratio (ICER) will be calculated with uncertainty around this characterised by plots on the cost-effectiveness plane and its associated cost-effectiveness acceptability curve. The impact of different training costs as observed in the different centres will be assessed using one-way sensitivity analysis.

